**Methods:**

In this Randomized Control Trial (RCT), 60 subjects with chemotherapy-induced cognitive impairments secondary to any cancer will be randomised into 2 groups by the sequentially numbered opaque sealed envelope approach. The cognitive functions will be measured as the outcome measures, which include all the recall strategies, executive function tasks, information processing speed, and attention.
Both groups will receive intervention every day for 4 weeks. Wilcoxon signed the rank test for data analysis, and students paired the “t” test, which will be used to study within-group effects. Mann-Whitney U Test and students Unpaired “t” Test will be used to compare groups at pre-treatment and post-treatment.

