## Methods

### Trial Design

This is an equal allocation, parallel-group, 2-arm superiority study, with the sample size distributed equally between the 2 groups. Patients will be evaluated according to predetermined inclusion and exclusion criteria and will be recruited from Siddharth Gupta Memorial Cancer Hospital in Sawangi, which is affiliated with Acharya Vinoba Bhave Rural Hospital. After obtaining informed consent, eligible participants will be selected through simple random sampling using computer-generated random numbers. All patients will be informed about the study procedures and asked to provide written consent before participation. The trial will include patients with a medical diagnosis of cancer who are currently undergoing chemotherapy. Sequence generation will be performed using computer-generated random numbers.

The allocation concealment mechanism will involve simple random sampling. Study participants will be randomly assigned using computer-generated random numbers. Randomization will be conducted by a researcher not involved in participant recruitment. To ensure allocation concealment, opaque sealed envelopes will be used, which will be opened only after participants are deemed eligible for treatment by the research team. Data collection will be carried out after participants are assigned to their respective intervention groups, with outcomes assessed and recorded during the preintervention phase. Postintervention data collection will be conducted after 4 weeks of intervention.

In data management, information obtained will be summarized using frequency and percentage for qualitative data, and mean and SD for quantitative data. Figure 1 presents the CONSORT (Consolidated Standards of Reporting Trials) flow diagram outlining the study design. See Multimedia Appendix 1 for the SPIRIT (Standard Protocol Items: Recommendations for Interventional Trials) checklist.

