### Selection of Participants

After obtaining ethical clearance from the Institutional Ethics Committee, patients diagnosed with cancer and scheduled to undergo chemotherapy will be identified at Siddharth Gupta Memorial Cancer Hospital. Permission will be sought from the treating residents, and eligible patients who meet the inclusion criteria will be enrolled after obtaining informed consent. Treatment will commence within 1 week of initiating the chemotherapeutic agent, and baseline data will be recorded. Participants will receive cognitive rehabilitation focusing on memory, attention, information processing, and executive function, with the aim of enhancing cognitive performance and improving quality of life. The first outcome measure, the Mini-Mental State Examination (MMSE), will be administered before the initiation of chemotherapy along with baseline data to assess cognitive function. Subsequently, the Montreal Cognitive Assessment will be conducted over 4 chemotherapy cycles. Participants will undergo the intervention 5 days per week, and following the completion of the 4 chemotherapy cycles, postintervention baseline data will be recorded. The outcome measures will be used to assess the degree of cognitive impairment. Follow-up assessments will be conducted after each chemotherapy cycle and weekly after completion of the intervention. Baseline outcome measures will be recorded after 4 chemotherapy cycles, and follow-up evaluations will be carried out once a week for 4 consecutive weeks.

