### Participant Timeline

Pre- and postbaseline data will be collected, followed by a 4-week intervention period. After the completion of the 4 weeks, postintervention outcomes will be assessed. The study design is illustrated in the CONSORT flowchart presented in Figure 1.

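### Outcomes are first recorded after arm assignment, and the protocol does not fix one baseline or secure a pre-intervention Montreal Cognitive Assessment

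*Protocol article*

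**What the plan says.** Four parts of the protocol article bear on when outcomes are first measured.

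- **Trial Design.** The opaque sealed envelope is opened once a participant has been found eligible. The section continues: "Data collection will be carried out after participants are assigned to their respective intervention groups, with outcomes assessed and recorded during the preintervention phase". Outcomes are measured again after 4 weeks of intervention.
- **Selection of Participants.** "Treatment will commence within 1 week of initiating the chemotherapeutic agent, and baseline data will be recorded". The MMSE is called the first outcome measure and "will be administered before the initiation of chemotherapy along with baseline data to assess cognitive function". The next sentence reads "Subsequently, the Montreal Cognitive Assessment will be conducted over 4 chemotherapy cycles". Later the same section says "Baseline outcome measures will be recorded after 4 chemotherapy cycles", and it also attaches the word baseline to a post-intervention recording.
- **Participant Timeline.** "Pre- and postbaseline data will be collected, followed by a 4-week intervention period".
- **Outcome Measures.** The primary outcomes are the MMSE, the Montreal Cognitive Assessment and FACT-Cog, which is a self-report questionnaire. The secondary outcomes are the QLQ-C30 and the self-reported Patient-Specific Functional Scale.

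On the use of the pre-treatment scores, the Abstract (Methods) plans paired tests within each group, and unpaired t and Mann-Whitney tests that "will be used to compare groups at pre-treatment and post-treatment". Trial Design and Statistical Analysis also specify an unpaired t test between groups, with a Mann-Whitney test for non-normal data. No change-score or baseline-adjusted comparison between groups is stated.

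**The concern.** Randomisation makes the arms comparable, apart from chance, on anything measured before allocation is known. It gives no such guarantee for a score taken after the participant has learned the arm. The two programmes cannot be mistaken for each other: the control programme is exercise and cognitive behavioral training without direct supervision, and the intervention adds domain-specific cognitive tasks, many of them led by a therapist. Disappointment or expectation can therefore move a questionnaire answer before any treatment is given.

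A participant who withdraws between the opening of the envelope and the first assessment contributes no outcome data at all. That works against the intention-to-treat analysis planned in Statistical Analysis.

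The Montreal Cognitive Assessment raises a second problem. Its only specific timing is during the 4 chemotherapy cycles, while the intervention starts within a week of chemotherapy. The first score may therefore come after the intervention has begun. A within-group pre/post test on such a score would miss whatever change had already occurred.

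**Working it through.** **1. The baseline statements side by side**

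| Place | When outcomes are recorded |
|---|---|
| Trial Design | After assignment, before the intervention |
| Selection of Participants, MMSE | Before chemotherapy starts |
| Selection of Participants, general baseline data | Around the start of treatment, itself within 1 week of starting chemotherapy |
| Selection of Participants, Montreal Cognitive Assessment | After the MMSE, over the 4 cycles |
| Selection of Participants, baseline outcome measures | After 4 cycles |
| Participant Timeline | Pre- and post-baseline data, both ahead of the 4-week intervention |

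These do not describe a single visit. Only the general wording of Trial Design would place a Montreal score before the intervention, and the sentence specific to that scale points later.

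**2. The plan's own yardstick**

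Inputs from Sample Size: d = 0.8, Z values 1.96 and 0.84, allocation 1:1.

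n = 2 × (1.96 + 0.84)² / 0.8² + 1.96² / 4 = 24.5 + 0.96 = 25.46, rounded up to 26 per group.

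The stated 26 is reproduced. Exact two-sided t-test power at d = 0.8 is 80.7% with 26 per group and 86.1% with 30. None of this depends on a baseline score. The value d = 0.8 is used below only as a scale for the bias.

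**3. Baseline shifted by knowledge of the arm**

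Assumptions, not in the document: the shift is s = 0.2 SD in one arm, and the correlation ρ between baseline and post-treatment scores is 0.5 to 0.7.

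- Post-treatment t test: no baseline term, so bias from the shift = 0.
- Within-group change in the shifted arm: off by s = 0.2 SD.
- Change-score contrast: bias = s = 0.2 SD; 0.2 / 0.8 = 25%.
- Baseline-adjusted contrast: bias = ρ × s. At ρ = 0.5 it is 0.10 SD and 0.10 / 0.8 = 12.5%. At ρ = 0.7 it is 0.14 SD and 0.14 / 0.8 = 17.5%.

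The bias is proportional to s. Half the shift (0.1 SD) gives 0.1 SD (12.5%) for the change score and 0.05 to 0.07 SD (6.25% to 8.75%) after adjustment. No shift gives none. The sign depends on which arm moves and in which direction, so the effect could be overstated or understated.

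**4. First Montreal score taken after the intervention has begun**

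Assumptions: a fraction f of the final effect is already present at the first score, and ρ is 0.3 to 0.7. A change-score contrast recovers 1 − f of the effect, and an adjusted contrast recovers 1 − ρf.

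| f | Change score | Baseline-adjusted | Post-treatment only |
|---|---|---|---|
| 10% | 90% | 93% to 97% | 100% |
| 25% | 75% | 82.5% to 92.5% | 100% |
| 50% | 50% | 65% to 85% | 100% |

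**The case against.** The strongest reply is that Trial Design places outcome recording before the intervention and makes no exception for the Montreal scale. Selection of Participants says that the MMSE is given together with baseline data, not that it is the only baseline measure. FACT-Cog, the QLQ-C30 and the Patient-Specific Functional Scale are not named there either, and nobody would conclude that they have no baseline. Figure 1 and the SPIRIT checklist are not shown and may contain a clear schedule. This stands: a reader might infer that the Montreal scale has no pre-intervention value at all, but that is only one reading of conflicting text.

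A reader might also call the baseline contaminated by treatment. Trial Design does not support that. Its risk is knowledge of the arm, not exposure to the intervention. Nor is a score taken during chemotherapy spoiled for that reason, since the trial enrols patients already on chemotherapy. What matters is its order relative to the intervention.

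Third, the stated between-group test compares post-treatment scores and needs no baseline. This also stands. One might add that the trial loses the variance reduction that adjustment would bring (ρ² = 25% to 49% at ρ = 0.5 to 0.7), but no adjustment is stated, so the plan as written does not count on it.

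What the reply does not remove is the stated order of assignment before measurement, the unsecured timing of the Montreal score, and the several incompatible uses of the word baseline.

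**Conclusion.** The point holds in a limited form. First outcome recording follows assignment, no text specific to the Montreal Cognitive Assessment secures a score before the intervention, and Trial Design, Selection of Participants and Participant Timeline do not yield one baseline.

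The harm falls on the within-group paired tests, the pre-treatment group comparison, and any change-score or baseline-adjusted analysis added later. In the pre-treatment comparison, a shift caused by knowledge of the arm could not be told apart from chance imbalance. The documents do not support the stronger conclusion that the post-treatment comparison between groups is biased by baseline timing.

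The size depends on assumed values. A 0.2 SD shift gives a bias of 25% of d = 0.8 for a change score and 12.5% to 17.5% after adjustment, and smaller shifts give proportionally less. The change should be made because it is cheap and removes the problem at its source; the main test is not invalid without it.

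**What to change.** Reconcile Trial Design, Selection of Participants and Participant Timeline into one defined baseline visit: consent, eligibility, all five outcomes (MMSE, Montreal Cognitive Assessment, FACT-Cog, QLQ-C30, Patient-Specific Functional Scale), then the envelope, then the intervention. Keep the word baseline for that visit and give the later assessments other names. Where the visit falls relative to the start of chemotherapy is for the sponsor to settle; the statistical requirement is only that it precede disclosure of the arm and the intervention.

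Results reports 60 participants enrolled by November 9, 2024, with data collection from November 14. Enrolled need not mean allocated, but reordering may no longer be possible for some or all of them. For anyone already allocated first:

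- keep them in the intention-to-treat analysis; excluding them would drop randomised participants, and could leave nobody if Trial Design was followed throughout;
- report how many had baseline measured after allocation, and whether each first Montreal score preceded the intervention;
- rest the conclusion on the post-treatment comparison between groups, not on within-group change.

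Cost: a reordered visit and one short extra test at baseline. Where allocation has already happened, the cost is a reporting item only.

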**Figure 1 figure1:**
[figure not shown]
CONSORT (Consolidated Standards of Reporting Trials) flow diagram.

Descriptive statistics will be used to analyze demographic variables such as age and gender. Measures including mean, SD, frequency (n, %), chi-square test, and independent *t* test will be applied to confirm the homogeneity of descriptive statistics. Inferential statistics between the 2 groups will be assessed using an unpaired (2-tailed) *t* test. All statistical analyses will be performed using SPSS software, version 21.0 (IBM Corp). For this study, a *P* value of less than .05 will be considered statistically significant.

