### Statistical Analysis

For demographic factors, all data will be summarized using baseline characteristics, expressed as the mean and SD for continuous data and as frequency and percentage for categorical data.

The analysis of outcome variables will primarily focus on continuous variables. For parametric data, the minimum, maximum, mean, SD, SE, and 95% CI will be summarized. The normality of continuous outcome variables will first be tested using the Kolmogorov-Smirnov test at a 5% level of significance (*P*≤.05). If the data are found to deviate from normality, a nonparametric test will be applied to determine significance. An independent *t* test will be conducted for group comparisons to assess significant differences at the 5% level (*P*≤.05). The intervention groups will receive (1) cognitive training supplementing traditional physical treatment and (2) traditional physical treatment.

The effect size at different assessment visits between the 2 groups will be calculated for the variables MMSE and Montreal Cognitive Assessment. For nonnormal data, descriptive statistics will include the mean, median, and lower and upper quartiles. The Mann-Whitney test will be applied to determine statistical significance when nonparametric methods are required.

Categorical variables will be summarized using frequency (n) and percentage. Chi-square analysis will be performed to evaluate efficacy across categorical variables. An intention-to-treat analysis will be applied to minimize attrition bias among participants, including those lost to follow-up or deceased due to adverse effects of chemotherapeutic drugs.

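### The between-group test leaves out the recorded baseline score; a baseline-adjusted comparison would gain precision, and the within-arm tests and the intention-to-treat wording need tidying

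*Protocol article*

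**What the plan says.** The statistics paragraph under Trial Design fixes the comparison of arms: "Inferential statistics between the 2 groups will be assessed using an unpaired (2-tailed", that is, a t test. The Statistical Analysis section agrees: "An independent *t* test will be conducted for group comparisons to assess significant differences at the 5% level". It makes the choice of test depend on a Kolmogorov-Smirnov test of the outcome: "If the data are found to deviate from normality, a nonparametric test will be applied to determine significance", and then "The Mann-Whitney test will be applied to determine statistical significance when nonparametric methods are required".

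The abstract gives the time points. The t and Mann-Whitney tests "will be used to compare groups at pre-treatment and post-treatment". It also names paired t and Wilcoxon signed-rank tests, which "will be used to study within-group effects". The Statistical Analysis section does not repeat the paired tests.

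No section names a baseline covariate, a change score or a repeated-measures model. Trial Design nevertheless says that outcomes are recorded before the intervention and again after 4 weeks.

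On the analysis set, the Statistical Analysis section says: "An intention-to-treat analysis will be applied to minimize attrition bias among participants, including those lost to follow-up or deceased" because of chemotherapy toxicity.

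**The concern.** Three things are at stake.

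- **Precision and imbalance.** A cognitive score after treatment usually correlates with the same score before it. A test that ignores the first score carries variance that could be removed at no cost. Trial Design describes simple randomisation with no stratification, for 60 patients aged 14 to 70 with a range of cancers and drugs. Some chance imbalance in baseline cognition is to be expected. The planned homogeneity tests can flag it but do not adjust for it.
- **Within-arm tests.** The change in one arm mixes treatment with practice on repeated tests and with ongoing chemotherapy. The first and third objectives ask for the effect of rehabilitation on cognition and on quality of life, separately from the comparison with conventional therapy. That wording leaves room to answer them from one arm's paired P value.
- **Intention-to-treat.** The promise covers people who may have no post-treatment score. A t or Mann-Whitney test, as named, uses only scores that exist.

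**Working it through.** **Inputs from the Sample Size section:** d = 0.8, two-sided 5% (z = 1.96), 80% power (z = 0.84), allocation 1:1, 26 evaluable per group, and 30 per group after 15% dropout. **Assumption:** the correlation ρ between baseline and post score is not in the documents, so I use 0.3, 0.5 and 0.7.

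**1. The plan's own figure.** n = 2 × (1.96 + 0.84)² / 0.8² + 1.96² / 4 = 24.5 + 0.96 = 25.46, rounded up to 26 per group. This reproduces. Exact power of the unadjusted t test at 26 per group uses the noncentral t distribution with 50 degrees of freedom and noncentrality 0.8 × √(26/2) = 2.88. It is 80.7%. The sample size therefore fits the stated test.

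**2. Adding the baseline score.** ANCOVA multiplies the residual variance by 1 − ρ², so d becomes 0.8 / √(1 − ρ²), with 2 × 26 − 3 = 49 degrees of freedom.

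| ρ (assumed) | Variance removed (ρ²) | Effective d | Noncentrality | Power, 26 per arm |
|---|---|---|---|---|
| unadjusted | 0% | 0.80 | 2.88 | 80.7% |
| 0.3 | 9% | 0.84 | 3.02 | 84.2% |
| 0.5 | 25% | 0.92 | 3.33 | 90.4% |
| 0.7 | 49% | 1.12 | 4.04 | 97.7% |

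**3. What two paired tests can show.** Suppose both arms change by the same true amount, so there is no treatment difference. Let p be the power of one paired t test (n = 26, 25 degrees of freedom, noncentrality = standardised change × √26). One arm is significant and the other not with probability 2p(1 − p).

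| Standardised change | p | 2p(1 − p) |
|---|---|---|
| 0.2 | 0.165 | 28% |
| 0.3 | 0.313 | 43% |
| 0.4 | 0.500 | 50% |
| 0.6 | 0.836 | 27% |
| 0.8 | 0.975 | 5% |

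The 50% is the mathematical maximum, reached at p = 0.5; the range is the result. The true change is also an assumption, since the documents give none.

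**4. Intention-to-treat against the named tests.** The Sample Size section inflates 26 to 30 so that 26 remain after dropout. The sizing thus treats dropouts as giving no outcome, while the Statistical Analysis section says that they are included. The article does not say how the two fit together.

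In a simulation under no treatment effect (30 per arm), 15% dropped out at random in one arm. In the other, dropout depended on baseline (assumed rates 27% below and 3% above the mean). The unadjusted comparison of observed scores was off by 0.054 SD at ρ = 0.5 and 0.078 SD at ρ = 0.7, with type I error of 5.7% and 5.5%. The baseline-adjusted estimate from the same data was within 0.002 SD of zero. The bias is small and needs this specific dropout pattern.

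**The case against.** The strongest reply is that nothing here is invalid. Under randomisation, without informative dropout, the unadjusted test keeps its error rate. Chance imbalance is already inside its standard error, and the trial is correctly sized for it. That stands: the loss is in precision, and its size rests on a correlation the documents do not give. At ρ = 0.3 the gain is only 3.5 percentage points of power (84.2 − 80.7).

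A reader might infer that the plan makes intention-to-treat impossible. The documents do not support that. A t or Mann-Whitney test can be run on everyone randomised once missing scores are imputed, and such rules may sit in an analysis plan that is not shown. ANCOVA at one visit would also drop people without a post score, so this gap lies in the handling of missing data and not in the lack of adjustment. It would likewise go too far to dilute the effect by scoring dropouts as no effect, because the protocol plans no such analysis.

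A reader might also infer that the trial will judge rehabilitation by paired tests. Only the abstract mentions them, and Trial Design declares superiority and assigns inference between groups to the unpaired test. The risk is misreading, not a stated decision rule.

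Lastly, the sections on inference do not say whether the tested variable is the post score or the change; only the abstract points to separate pre- and post-treatment comparisons. That is a fair caveat, but on either reading no baseline covariate is named.

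**Conclusion.** The point holds as an avoidable inefficiency plus two matters of wording; it is not an invalid analysis. Adjusting for baseline removes 9%, 25% or 49% of residual variance at assumed correlations of 0.3, 0.5 or 0.7. Power at the planned effect rises from 80.7% to 84.2%, 90.4% or 97.7% with the same patients. Adjustment also corrects chance baseline imbalance, which the planned test leaves in the estimate.

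The paired tests cannot support a claim about treatment: under equal true change they disagree between arms in 5% to 50% of trials over standardised changes of 0.2 to 0.8.

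The intention-to-treat promise and the named tests do not fit together as written. The document supports no stronger statement than that. The change is worth making before outcomes are analysed.

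**What to change.** 1. For each outcome, make the between-group analysis an ANCOVA of the 4-week post-intervention score on treatment and the baseline score of the same instrument. Report the adjusted difference with its 95% CI.
2. Replace the switch that depends on a normality test with a rank-based version of the same model as a sensitivity analysis.
3. Report within-arm changes descriptively, without P values, and align the abstract.
4. Settle the visit schedule first. Trial Design and Participant Timeline give one assessment after 4 weeks; Selection of Participants gives assessments after each chemotherapy cycle and weekly afterwards. If the repeated visits are confirmed, a mixed model on them can include every randomised participant with any post-baseline score. If not, describe the analysis set as all randomised participants with an observed score.
5. Report deaths separately and do not impute scores after death.

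**Cost:** a little more analysis work, with no extra patients. Each instrument must be recorded at baseline. Selection of Participants is unclear on this for the Montreal Cognitive Assessment: it places the Mini-Mental State Examination before chemotherapy and the Montreal test afterwards, over the cycles.
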